### Power calculation

Previous trials of stage-based interventions for smoking cessation [53–57] and trials of Internet interventions for smokers motivated to quit [11, 58] suggest that quit rates for motivated smokers may be as high as 20 % (treatment) and 9 % (control). However, as this will be the first stage-based intervention for young adult smokers delivered over Facebook, and cessation rates in some Internet trials have been as low as 7 % point prevalence abstinence at 3 month follow-up [59], the conservative estimate of 10 % (treatment) and 5 % (control) 7-day point prevalence abstinence at 3, 6, and 12 months follow-up was made. Further, attrition in Internet cessation trials has tended to be as high as 50–75 % at 3 and 6 months follow-up [11, 12, 59]. With 50 % attrition at each time point, and at least one covariate (depending on group differences), a sample size of 480 will provide a minimal power level of .80, and a Type-I error rate of .05 to detect these cessation rates in the most conservative outcome of the study - 7-day point prevalence abstinence.

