## Methods/Design

### Overview of design

This study is a randomized controlled trial (RCT) with 480 young adults age 18 to 25 recruited through Facebook (Fig. 1). Participants are randomized to one of two conditions: (1) the Tobacco Status Project motivationally-tailored smoking cessation intervention delivered through Facebook (TSP); or (2) a control condition (referral to the Smokefree.gov website). Assessments are conducted online at baseline, 3-, 6-, and 12-months follow-up. Primary outcome is biochemically-verified 7-day point prevalence abstinence from tobacco, and secondary outcomes are reduction in cigarettes smoked per week, 24 h quit attempts, and commitment to abstinence in each time period. Within the TSP group, a monetary engagement will be tested as a moderator of engagement and abstinence.

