### Data analysis

#### Primary analyses

Preliminary analyses will describe and summarize all measures and test the correlation between order of study entry and outcome rates of dropout by condition. If differences for any of these variables are noted, they will be statistically controlled as covariates in model testing. Missing data will be minimized through online assessment. When subjects do not complete online assessments, they will be re-contacted through Facebook or email to obtain missing information. For each hypothesis test, two sets of outcome analyses will be conducted - one with all participants who are maintained in the study, and another based only on biochemically verified smoking abstinence rates to allow for direct comparison of findings with the research literature.

The primary outcome of biochemically-verified 7-day abstinence will be compared between participants in the TSP and Control groups at 3- through 12-months follow up using a mixed-effects statistical model [60, 61]. The independent variables will be intervention versus the control condition, assessment point, plus covariates identified in preliminary analysis. The model will be estimated using maximum likelihood estimation.

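### The stated power of .80 does not follow from its own inputs: two-sided power is about 0.31 at one visit and at most 0.72 for the planned three-visit model

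*Protocol article*

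**What the plan says.** The Power calculation section of the protocol article takes "the conservative estimate of 10 % (treatment) and 5 % (control) 7-day point prevalence abstinence" at 3, 6 and 12 months as its planning rates. It adds the condition "With 50 % attrition at each time point", allows for at least one covariate, and concludes that "a sample size of 480 will provide a minimal power level of .80", with "a Type-I error rate of .05", "to detect these cessation rates in the most conservative outcome of the study - 7-day point prevalence abstinence". The Overview of design makes clear that 480 is the total for both arms: "This study is a randomized controlled trial (RCT) with 480 young adults age 18 to 25 recruited through Facebook".

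Under Primary analyses, the arms are compared over the three follow-ups with a mixed-effects model fitted by maximum likelihood. Two sets of analyses are planned, "one with all participants who are maintained in the study" and another restricted to biochemically verified abstinence. The article does not give the sidedness of the test, the allocation ratio, the within-person correlation or the strength of the covariate. It has no rule that counts missing participants as smokers.

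**The concern.** A difference of 5 percentage points between two low rates usually needs several hundred analysed participants per arm. Here, 480 in total with half lost leaves about 120 per arm at each visit, so .80 looks too high for the stated inputs. This is not a matter of detail left to a fuller document: the article prints the power together with inputs that contradict it.

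The figure is the sample-size justification for the primary outcome. The article calls the rates conservative and the power minimal. A reader would therefore take a null result as coming from a trial with at least a four-in-five chance of detecting the planned effect, when the real chance is materially lower.

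**Working it through.** **Inputs.** From the Power calculation section: 480 randomised, 10% versus 5%, 50% attrition per time point, alpha .05. Assumed: 1:1 allocation and a two-sided test (one-sided also shown). Observed per arm and visit: 480 / 2 × 0.5 = 120.

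**Formula.** Normal approximation with pooled variance under the null hypothesis, p̄ = 0.075:

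power = Φ( [ |p1 − p2|·√n − z·√(2p̄(1 − p̄)) ] / √(p1(1 − p1) + p2(1 − p2)) )

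**1. The article's own figure, single visit.** With n = 120: (0.05 × 10.954 − 1.96 × 0.3725) / 0.3708 = (0.548 − 0.730) / 0.3708 = −0.49, so power = 0.31. The arcsine and log-odds-ratio approximations give 0.32 and 0.30. The stated .80 is not reproduced.

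| n per arm, one visit | Two-sided | One-sided |
|---|---|---|
| 120 (50% attrition) | 0.31 | 0.43 |
| 240 (no attrition) | 0.55 | 0.67 |

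Two-sided 80% power at one visit needs 435 per arm analysed, or 870 in total. At 50% attrition that is 870 / 0.5 = 1740 randomised.

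**2. The planned three-visit model.** With the same treatment effect at each visit and within-person correlation ρ, the effective n per arm depends on the dropout pattern:

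- Same half lost throughout: 3 × 120 / (1 + 2ρ).
- Each visit missed independently with probability 0.5: 240 × Σ C(3,k)/8 × k / (1 + (k − 1)ρ), for k = 1, 2, 3.
- No attrition: 3 × 240 / (1 + 2ρ).

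Two-sided power (effective n per arm):

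| ρ | Same people lost | Missed independently | All 480 at all visits |
|---|---|---|---|
| 0 | 0.72 (360) | 0.72 (360) | 0.95 (720) |
| 0.3 | 0.52 (225) | 0.62 (285) | 0.81 (450) |
| 0.5 | 0.44 (180) | 0.57 (255) | 0.72 (360) |
| 0.7 | 0.38 (150) | 0.54 (233) | 0.64 (300) |
| 1 | 0.31 (120) | 0.49 (210) | 0.55 (240) |

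**3. Where .80 can be reached.**

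- Two-sided, with the stated attrition: not at any ρ ≥ 0.
- Two-sided, with all 480 at three visits: 720 / (1 + 2ρ) ≥ 435 gives ρ ≤ about 0.33.
- One-sided, with the stated attrition: 343 per arm are needed. If the same people are lost, 360 / (1 + 2ρ) ≥ 343 gives ρ ≤ about 0.02. If visits are missed independently, the limit is about 0.05.

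**4. Detectable rate at one visit, against 5%, 80% power, two-sided.** About 16% with 120 per arm and about 12% with 240 per arm.

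**5. Which denominator the rates refer to.** If 10% and 5% are rates among all randomised and all 480 are analysed, single-visit power is 0.55. If they are completer rates and missing participants were counted as smokers, the rates become 5% and 2.5% in 240 per arm, and power is about 0.30.

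**The case against.** The strongest objection is that 0.31 belongs to one visit, whereas the planned analysis uses three. That stands. A reader might infer that the trial's power simply is 0.31, or that its chance of success lies between one in three and one in two. The documents do not support either reading. With the stated attrition the planned model lies between 0.31 and 0.72, depending on the correlation and the dropout pattern, neither of which is given. The article plans to re-contact people who miss an assessment, so the more favourable pattern of independently missed visits cannot be excluded. Both patterns stay below .80.

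A reader might also infer that no assumption at all restores .80. That is too absolute, because sidedness is not stated: a one-sided test with near-zero correlation gives up to 0.82. But near-zero correlation between repeated abstinence measures in the same person is implausible. A negative correlation, which could also reach .80, is still less plausible.

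Counting missing participants as smokers would bring all 480 into the analysis. The article states no such rule, and its gain depends on what the assumed rates denote (step 5 of the working). A covariate might add some precision, but its strength is not given, its inclusion depends on group differences, and it is not a credible way to close a gap of this size.

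It is also tempting to say that even the optimistic 20% versus 9% is underpowered, since it gives 0.68 at one visit with 120 per arm. Over three visits with the same people lost, however, it gives 0.91, 0.85 and 0.77 at correlations 0.3, 0.5 and 0.7, and the article claims no power for those rates. That argument should not be used.

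**Conclusion.** The concern holds. For 10% versus 5% with 480 randomised, 50% attrition and two-sided alpha .05, power is about 0.31 at one visit. For the three-visit model it is roughly 0.4 to 0.6 at correlations of 0.3 to 0.7, with a ceiling of 0.72. The claimed .80 appears only if the stated attrition is set aside or if a one-sided test is combined with almost no within-person correlation.

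The conclusion assumes 1:1 allocation, non-negative within-person correlation, a constant treatment effect over time and no sizeable gain from covariates. The intervention is delivered in Facebook groups of about 10. Positive correlation within groups would lower power further, but the article gives no intraclass correlation, so this remains an unquantified caveat. The statement needs correction because it is the quantitative basis for the sample size.

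**What to change.** Keep 480 and restate the power. The statement should name the analysis it refers to (single visit or averaged over time), the sidedness, the within-person correlation, and whether 10% and 5% are rates among all randomised or among completers. Suggested wording:

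> With 480 randomised 1:1 and 50% attrition at each time point, two-sided power for 10% versus 5% is about 0.31 at one visit, and about 0.4 to 0.6 for the three-visit model at within-person correlation 0.3 to 0.7. Against 5%, the rate detectable with 80% power at one visit is about 16% with 120 per arm.

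The single-visit power of 0.55, with a detectable rate of about 12%, should be quoted only if all 480 are analysed and the assumed rates apply to all randomised. If so, the rule for missing outcomes must be stated alongside it. Clustering by Facebook group should be noted as a factor that could lower these figures.

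The cost is wording only: the stated power becomes less favourable, and no enrolment is added.

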### Data analysis

#### Primary analyses

Preliminary analyses will describe and summarize all measures and test the correlation between order of study entry and outcome rates of dropout by condition. If differences for any of these variables are noted, they will be statistically controlled as covariates in model testing. Missing data will be minimized through online assessment. When subjects do not complete online assessments, they will be re-contacted through Facebook or email to obtain missing information. For each hypothesis test, two sets of outcome analyses will be conducted - one with all participants who are maintained in the study, and another based only on biochemically verified smoking abstinence rates to allow for direct comparison of findings with the research literature.

The primary outcome of biochemically-verified 7-day abstinence will be compared between participants in the TSP and Control groups at 3- through 12-months follow up using a mixed-effects statistical model [60, 61]. The independent variables will be intervention versus the control condition, assessment point, plus covariates identified in preliminary analysis. The model will be estimated using maximum likelihood estimation.

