### Study procedure

Informed consent is obtained from all study participants in accordance with the Helsinki Declaration and approved by the UCSF Committee in Human Research (#11-06294). During the informed consent process, participants’ understanding of the information provided is assessed through a series of multiple choice questions with required responses before being able to proceed with the study. Questions are based on those used in studies with potentially vulnerable populations [41, 42]. Any wrong answers during the consent process are sent to study staff who then contact a potential participant via email or Facebook for further clarification of the consent process. Therefore, no participant will be enrolled that has not answered all consent questions correctly. Participants consenting to participate in the study are asked to verify age by sending proof through email or social media. Verified participants are emailed a baseline assessment. Those completing the baseline assessment are randomized to receive either the Tobacco Status Project (TSP) intervention of referral to the Smokefree.gov website (control).

A stratified random assignment program was developed and participants are assigned from within stratified blocks immediately after completing the baseline assessment. Participants are stratified on stage of change (precontemplation, contemplation, preparation) and smoking pattern (daily vs. non-daily), variables known to be related to outcomes and addressed by the intervention [43]. Participants in the TSP group are assigned to “secret” (private) Facebook groups based on their readiness to quit tobacco. Groups begin when there are approximately 10 participants enrolled, as that has been deemed the optimal number based on analyses of engagement in our previous work [37] ([name], [name], [name]: Smoking cessation intervention on Facebook: Which content generates the best engagement?, submitted). Participants in the control condition are given a referral to the Smokefree.gov program and are encouraged to use it as much as they would like.

Assessments occur online using the survey program Qualtrics at baseline, 3, 6, and 12 months follow-up. Participants receive their choice of gift cards in the amount of $20 per assessment, and a $20 bonus for completing all three assessments, for a total possible stipend of $100 for completing all assessments.

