### Secondary analyses

Mixed effects logistic and multinomial regression models for longitudinal ordinal response data to model secondary outcomes for tobacco use and across time (3, 6, 12 months): 1) reduction of cigarettes by 50 % or more (y/n), 2) tobacco quit attempt (y/n; 2 models), 3) action or maintenance stage of change (y/n); and 4) commitment to abstinence (y/n). Independent variables in all models will be treatment condition, abstinence status, and covariates identified as relevant to smoking characteristics in the literature.

To evaluate the secondary aim (effect of a monetary incentive on engagement in the TSP condition), we will test for differences in engagement and primary smoking outcome by incentive groups and the relationship between engagement and primary smoking outcome at 3 months. First, due to expected skewed distribution of the engagement variable (comments), the non-parametric Kruskal-Wallace test will examine overall differences in total number of comments made to the Facebook study group by incentive condition, with test for a linear trend in commenting by incentive frequency. Second, Pearson’s chi-square test will examine 7-day point prevalence abstinence by incentive condition. Abstinence rates will be examined by incentive group. Two sets of analyses will be conducted: one for biochemically verified abstinence, and one for reported abstinence. Finally, Mann–Whitney U tests will compare comments for those abstinent at 3months to those non-abstinent. Again, two sets of analyses will be conducted (one for biochemically-verified abstinence and one for reported abstinence).

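### The primary model's covariates are chosen after a look at the data, with dropout a likely trigger, while the two randomisation strata are not named in the model

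*Protocol article*

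**What the plan says.** Protocol article, Primary analyses. The preliminary work summarises all measures and will "test the correlation between order of study entry and outcome rates of dropout by condition". The next sentence gives the rule: "If differences for any of these variables are noted, they will be statistically controlled as covariates in model testing". The primary mixed-effects model is then defined: "The independent variables will be intervention versus the control condition, assessment point, plus covariates identified in preliminary analysis".

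Power calculation. The sample size allows for "at least one covariate (depending on group differences", so the number and identity of the covariates are left to the observed data there too.

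Study procedure. "Participants are stratified on stage of change (precontemplation, contemplation, preparation) and smoking pattern (daily vs. non-daily), variables known to be related to outcomes". Allocation is blocked: "participants are assigned from within stratified blocks immediately after completing the baseline assessment". Neither factor is named as a term in the primary model.

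Secondary analyses. The models for the secondary outcomes use a different rule: "covariates identified as relevant to smoking characteristics in the literature". That rule does not cover the primary outcome.

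**The concern.** Three things follow from these statements.

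- **The primary model is open.** No test, threshold or candidate list defines a difference. Two analysts following the text could fit different primary models, and each would choose covariates after seeing data that include condition.
- **One trigger appears to be a post-randomisation variable.** Dropout can be affected by treatment: one arm gets 90 days of Facebook posts and live sessions, the other a website referral. Conditioning on a consequence of treatment can move the treatment estimate in either direction. The plan assumes 50% attrition at each visit, so this is not a remote case. Order of study entry, the other trigger named, is fixed before randomisation and raises no such problem.
- **The rule looks in the wrong place for prognostic factors.** A covariate is worth including because it predicts outcome. Stage and smoking pattern are described as doing so, yet blocking within strata makes a difference between arms on them unlikely.

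**Working it through.** **Which figures bear on this.** The rule itself carries no number. The nearest stated figure is power .80 for 10% versus 5% with 480 participants (Power calculation). With pooled variance, a two-sided 5% test at one visit and 1:1 allocation (assumed; the ratio is not stated), 240 per arm gives:

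- SE under the null = √(2 × 0.075 × 0.925 / 240) = 0.0240
- SE under the alternative = √((0.10 × 0.90 + 0.05 × 0.95) / 240) = 0.0239
- power = Φ((0.05 − 1.96 × 0.0240) / 0.0239) ≈ 0.548

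With 120 per arm (50% attrition) the result is 0.311. That these fall short of .80 is a separate matter. They serve here only as a reference for the simulation below.

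**Step 1: effect of a dropout covariate.** Inputs: 10% and 5% abstinence (Power calculation). Assumptions: missing counted as smoking; dropout of 40% in one arm and 60% in the other, averaging the planned 50%; one visit.

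- True odds ratio = (0.10/0.90) / (0.05/0.95) = 2.11.
- Every dropout is then a non-abstainer. The dropout coefficient runs to minus infinity, those participants stop contributing to the likelihood, and the treatment coefficient is estimated from completers alone.
- Dropout 40% TSP, 60% control: 0.10/0.60 = 16.7% versus 0.05/0.40 = 12.5%. OR = (0.167/0.833) / (0.125/0.875) = 1.40.
- Dropout 60% TSP, 40% control: 0.10/0.40 = 25.0% versus 0.05/0.60 = 8.3%. OR = (0.25/0.75) / (0.083/0.917) = 3.67.
- Dropout 50% in both: 20% versus 10%, OR = 2.25.

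With equal dropout the shift is small, and the rule would not be triggered. It would be triggered when dropout differs, which is when the distortion is largest.

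**Step 2: effect of leaving out the strata.** Single-visit logistic simulation with 3000 trials per setting, 1:1 allocation within six strata, marginal rates of 5% and 10%, and a two-sided Wald test at 1.96. Model without strata: intercept and condition. Model with strata: plus two stage indicators and one smoking-pattern indicator. Assumed, because the article gives no values: stage shares 35/35/30%, 80% daily smokers, and the prognostic odds ratios in the table (preparation versus precontemplation; non-daily versus daily).

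| Total N | Stage OR / non-daily OR | Type I error without → with strata | Power without → with strata |
|---|---|---|---|
| 480 | 1 / 1 | 0.045 → 0.045 | 0.519 → 0.521 |
| 480 | 3 / 1.5 | 0.041 → 0.043 | 0.527 → 0.536 |
| 480 | 6 / 2 | 0.043 → 0.046 | 0.528 → 0.550 |
| 480 | 15 / 3 | 0.032 → 0.039 | 0.530 → 0.568 |
| 240 | 1 / 1 | 0.033 → 0.035 | 0.290 → 0.297 |
| 240 | 3 / 1.5 | 0.027 → 0.030 | 0.284 → 0.297 |
| 240 | 6 / 2 | 0.028 → 0.034 | 0.281 → 0.302 |
| 240 | 15 / 3 | 0.025 → 0.036 | 0.269 → 0.309 |

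The rows with no prognostic effect (0.519 and 0.290) lie near the closed-form 0.548 and 0.311. Where the strata matter, including them adds about 1 to 4 points of power. Without them type I error stays below 5%. Monte Carlo standard error is about √(0.55 × 0.45/3000) = 0.009 for power and √(0.04 × 0.96/3000) = 0.004 for type I error; both models were fitted to the same simulated trials.

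A second simulation (1500 trials, stage shares 35/45/20%, 75% daily, control abstinence about 1.5%, 4% and 12% by stage) gave power 0.57 → 0.60 and type I error 0.039 → 0.045, in the same direction.

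**Step 3: sparseness.** Expected abstainers per visit are 240 × (0.10 + 0.05) = 36, or 18 at 50% retention. Under the second simulation's assumptions, control participants in precontemplation supply 240 × 0.35 × 0.015 ≈ 1.3 events, or about 0.6 at half retention.

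**The case against.** **The sentence on dropout is garbled.** Words seem to be missing, and the variables to be controlled could be dropout, order of entry, or the measures on which differences appear. This stands in part. A reader might infer that the plan definitely adjusts for dropout; the text supports only that this is its natural reading.

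**The bias needs an assumption the article does not make.** Counting missing as smoking is nowhere stated, and one of the two analysis sets is limited to participants who stay in the study. Dropout at a visit does not vary among those seen at that visit, so it could not act as a covariate there. This stands, and step 1 is an illustration only. A reader might also infer that the bias has no limit, since dropout would predict non-abstinence perfectly. That does not follow: only the dropout coefficient diverges, and the treatment odds ratio settles at the completers' value.

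**The strata might still enter.** All measures are summarised, blocking balances those randomised and not those retained, and stage could be flagged through an association with dropout. This stands. A reader might infer that the rule can never select the strata; the documents support only that it is unlikely to.

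**The loss is small.** This also stands. A reader might infer that omitting the strata invalidates the test, but the simulations show a conservative test with a modest loss of power. They use one visit and no random effect, whereas the plan is a three-visit mixed model.

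**A condensed article may leave the covariates to the analysis plan.** This would answer a silence. Here the article states the selection rule and the model terms, and the power section repeats the rule. An analysis plan that followed it would carry the fault over; one that fixed the strata would contradict it.

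**Conclusion.** The point holds in this form: the primary covariate set is left to observed differences, probably including dropout by condition, and the two stratification factors are not named in the model. The open model and the possible post-randomisation covariate are the weightier parts.

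The size of any dropout bias depends on missing being counted as smoking and on how far dropout differs between arms; the range of 1.40 to 3.67 around 2.11 belongs to a 20-point difference in dropout. The 1 to 4 points of power depend on assumed prognostic strengths and stage shares, with no type I error inflation. The effect of the data-driven selection itself was not quantified, because the article gives no test or threshold to simulate. The change should be made, but nothing here shows that the trial's conclusions would be invalid without it.

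**What to change.** In Primary analyses, delete the rule that adds covariates when differences are noted. Prespecify baseline stage of change (three levels) and smoking pattern (daily or non-daily) as main effects in the primary mixed model, beside condition and assessment point. State that dropout by condition will be reported and used only to inform missing-data sensitivity analyses, never as a covariate. Bring the covariate wording in Power calculation into line.

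Both factors are known before randomisation, so no new data are needed and the change is one of wording. There is a small statistical cost: three extra parameters (two for stage, one for smoking pattern) with few events in some strata. A fallback for non-convergence, such as collapsing stage levels in a stated order, should therefore be written down in advance.

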Based on this formative work, we developed the *Tobacco Status Project (TSP),* a Facebook intervention for young adult smokers combining Facebook contacts tailored to participants’ readiness to quit smoking with a 12-week cessation program consisting of 90 days of Facebook postings, weekly counseling sessions, and for those ready to quit, 7 state-of-the-art group cognitive-behavioral sessions. A feasibility trial enrolled 79 young adults who formed 7 Facebook groups [36]. Follow-up rates were 84 and 72 % at 6 and 12 months, respectively, and reported 7-day abstinence was 21 % at 6 months (9 % biochemically-verified) and 18 % at 12 months (9 % verified) ([name], [name], [name], [name]: Feasibility and quit rates of the “Tobacco Status Project”, submitted). From baseline to 12-months, there was a significant increase in the proportion prepared to quit (13 to 46 %, p < .001), 35 % reduced their cigarette consumption by 50 % or greater, and 67 % reported a 24-h quit attempt. Engagement in the intervention was high, with 92 % participation in the full 3 month intervention and 61 % commented on at least one post, with more commenting among those randomized to receive a personal monetary incentive [37]. Participants reported reading most of the Facebook posts (mean usability rating = 3.3/4) and interactions from counseling sessions (3/4), thinking about what they read (3/4) and would recommend the program to others (3.3/4). Herein, we describe a randomized controlled trial testing the efficacy of TSP against a referral control condition with 480 young adult smokers who use Facebook.

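### One of the two analyses planned for every hypothesis is confined to retained participants and the other has no stated denominator, so no all-randomised analysis is fixed despite 50% planned attrition

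*Protocol article*

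**What the plan says.** Protocol article, Data analysis, Primary analyses: "For each hypothesis test, two sets of outcome analyses will be conducted", namely "one with all participants who are maintained in the study, and another based only on biochemically verified smoking abstinence rates". The stated reason for the second set is comparability with the literature. The next paragraph compares verified 7-day abstinence between TSP and control at 3 to 12 months in a mixed-effects model fitted by maximum likelihood. It does not say who is included.

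The same section gives three safeguards: assessment online, re-contact of non-responders, and a preliminary test of dropout by condition, with any difference entered as a covariate.

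Power calculation: the assumed rates are "the conservative estimate of 10 % (treatment) and 5 % (control) 7-day point prevalence abstinence at 3, 6, and 12 months follow-up". The section allows for 50% "attrition at each time point, and at least one covariate (depending on group differences") and cites attrition of 50–75% in other Internet cessation trials.

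Measures, Primary outcome: a participant who reports 7-day abstinence and has salivary cotinine below 11 ng/ml is a confirmed non-smoker. Users of electronic nicotine delivery systems (ENDS) are reported separately. The section does not say how a person with no survey or no returned kit is counted.

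Background: follow-up in the feasibility trial was 84% at 6 months and 72% at 12 months.

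**The concern.** Randomisation protects a comparison of everyone randomised. It does not protect a comparison of those who go on answering surveys. If people who still smoke are likelier to stop responding, and the arms lose them at different rates, abstinence among those retained differs between arms without any treatment effect. A real effect can be masked in the same way.

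Unequal retention is plausible here. TSP participants receive 90 days of posts, weekly live sessions and, in three of the four incentive conditions, up to $90 for commenting. Control participants receive one referral. Payment for assessments is described without any difference by arm, but contact with the study clearly differs. The main efficacy claim is at stake.

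This is more than detail left to an analysis plan. The article positively fixes a retained set for every hypothesis test, and an analysis plan that made all randomised participants primary would have to depart from or add to that text.

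**Working it through.** **Inputs.** From the Power calculation section: N = 480, 10% versus 5%, attrition 50%, alpha .05. From Background: follow-up of 84% and 72%. Assumptions: 1:1 allocation (240 per arm), a two-sided test, and all retention splits by arm.

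**The plan's own figure.** The Power calculation section states that "a sample size of 480 will provide a minimal power level of .80, and a Type-I error rate of .05". With 50% lost, 240 × 0.5 = 120 per arm remain at a visit. For a pooled two-proportion test:

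- null SE = √(2 × 0.075 × 0.925 / 120) = 0.0340
- alternative SE = √((0.10 × 0.90 + 0.05 × 0.95) / 120) = 0.0339
- power = Φ((0.05 − 1.96 × 0.0340) / 0.0339) = Φ(−0.49) ≈ 31%

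The stated .80 is not reproduced by this single-visit test. That is a separate matter, and the present point does not depend on it.

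**False positives when dropout depends on smoking.** Let p be true abstinence in both arms, r the arm's overall retention, and suppose every abstainer is followed up. Then:

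- rate among those retained = p / r
- retention of smokers = (r − p) / (1 − p)

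With p = 0.05 and r = 0.50, for example, the observed rate is 0.05 / 0.50 = 10.0% and smoker retention is 0.45 / 0.95 = 47.4%. The rejection rates below come from 400,000 simulated trials per row: 240 per arm, pooled z-test at one visit, two-sided 5%.

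| Retention, TSP vs control | Rate among retained | Rejects, retained set | Rejects, all randomised |
|---|---|---|---|
| 50% vs 50% | 10.0% vs 10.0% | 5.0% | 4.9% |
| 50% vs 70% | 10.0% vs 7.1% | 14.4% | 4.8% |
| 70% vs 50% | 7.1% vs 10.0% | 14.5% | 4.9% |
| 40% vs 60% | 12.5% vs 8.3% | 19.0% | 4.8% |
| 50% vs 60% | 10.0% vs 8.3% | 7.6% | 4.8% |
| 72% vs 84% | 6.9% vs 6.0% | 6.9% | 4.8% |

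The last row borrows the feasibility trial's 12- and 6-month follow-up as if they were two arms, purely to show a realistic level of retention. The second and third rows show that the direction of bias follows the direction of the retention gap.

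**A real effect hidden.** Take true rates of 10% (TSP) and 5% (control). TSP retains 60% of everyone. Control retains 80% of abstainers and 40% of smokers. Among those retained:

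- TSP: 0.10 × 0.6 / 0.6 = 10.0%
- Control: 0.05 × 0.8 / (0.05 × 0.8 + 0.95 × 0.4) = 0.04 / 0.42 = 9.5%

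**The safeguards.** Re-contact reduces loss but sets no rule for what is still missing. A covariate for dropout cannot bring back people who are outside the set. The maximum likelihood model uses partial follow-up validly if data are missing at random. It does not protect against dropout that depends on current smoking, and a participant with no follow-up contributes no outcome to it.

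**The opposite rule.** Counting the missing as not abstinent also has a failure mode. With 10% abstinent in both arms, dropout unrelated to smoking and retention of 70% versus 50%, the observed rates are 0.10 × 0.70 = 7% and 0.10 × 0.50 = 5%. The all-randomised test then rejects 14.7% of the time, and the retained-set test 5.0%.

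**The case against.** The strongest reply is that the primary outcome is verified abstinence, so the second set may be the primary one, and nothing says that it excludes anyone. This is partly right. A reader might infer that neither set contains all randomised participants and that the randomised comparison is lost. The text does not support that: the second set's denominator is unstated, not shown to be restricted. What remains is that no passage fixes an all-randomised analysis, while one passage fixes a retained one.

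A reader might also infer that half the sample is dropped. The 50% is a planning figure for each visit, and a model over three visits uses anyone with at least one follow-up. The feasibility trial lost only 16% at 6 months and 28% at 12 months.

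Nor do the documents show that the bias would favour TSP. Greater contact suggests, if anything, higher TSP retention, which in this set-up works against TSP. The $90 is paid for comments, not assessments.

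The feasibility gap between reported (21%) and verified (9%) abstinence at 6 months does not show that the endpoint is undefined, because Measures fixes it as verified. Only the handling of missing kits is open.

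Finally, the rejection rates use a single-visit test, full follow-up of abstainers and assumed gaps. With gaps of 10 to 12 points they are modest.

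**Conclusion.** The point holds in this form: the plan fixes a retained-participant analysis for each hypothesis, leaves the denominator of the verified analysis unstated, and so commits to no all-randomised comparison while planning for heavy attrition. The resulting bias can go either way. With no true effect and a nominal 5% test, false positives are about 7–8% at retention gaps of 10–12 points and about 14–19% at 20 points, against about 5% with all randomised as denominator.

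These sizes rest on 240 per arm, 5% true abstinence, complete follow-up of abstainers and a test at one visit. They show what the rule permits and do not predict what will happen in this trial. If retention is equal across arms, the false-positive rate stays at about 5%.

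**What to change.** State that the primary comparison is verified 7-day abstinence among all 480 participants in their assigned arms. Verified means reported abstinence plus cotinine below 11 ng/ml, with the separate reporting of ENDS users in Measures kept. A missing survey or missing kit counts as not verified.

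Prespecify two sensitivity analyses: multiple imputation by arm, using the baseline strata and earlier smoking status, and a tipping-point analysis over the missing outcomes. Claim efficacy only if the conclusion is robust to both. Keep the retained set as supportive.

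The change costs wording and standard analyses, and no new data. It has two downsides. Reported quit rates fall in both arms. Counting the missing as not verified is itself biased when retention differs by arm for reasons unrelated to smoking (about 15% false positives in the case worked above), so it should not stand without the sensitivity analyses.
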